### Participant timeline {13}

Study Flow Diagram

**Table Tabb:** 

Activity	Time (month)											
	1	2	3	4	5	6	7	8	9	10	11	12
Providing materials	*	*	*	*								
Entrance of patients					*	*	*					
Implementation								*	*			
Analysis of data										*		
Reporting final paper											*	*
Total	*	*	*	*	*	*	*	*	*	*	*	*

### Sample size {14}

The number of samples considering the type I error *α* = 0.05 and the type II error *β* = 0.20 with 80% test power and standardized effect size equal to *Δ* = 30 of the following formula based on to detect the inflammation effect based on changes in CRP (as the main outcome of this study) by l-carnitine supplementation (control group: 99.96 ± 33.16, intervention group: 98.48 ± 37.01) using the findings of Noormandi et al. CRP index (mg/dl) [25]:
$$ n=\frac{2\left[{\left({Z}_{1-\frac{\alpha }{2}}+{Z}_{1-\beta}\right)}^2\times {S}^2\right]}{\varDelta^2}=\frac{2\left[{\left(1.96+0.84\right)}^2\times {(37)}^2\right]}{30^2}=23.85 $$

The required sample size in each group has been equal to 24 people, and with considering the drop out patients, the sample size will be practically 30 patients in every group, which we will consider a total of 60. It seems that this sample size is small; however, several articles which conducted among ICU patients used a small sample size based on a formula like our ones and worked on about 60 patients [26–28].

### Recruitment {15}

Patients will be recruited from the specimens admitted to Al-Zahra hospital, Iran, Isfahan, a referral center in central of Iran.

### Assignment of interventions: allocation

#### Sequence generation {16a}

Each patient will be recruited into intervention or control group using a random number generating website: https://www.sealedenvelope.com/simple-randomiser/v1/lists. Eligible patients will be randomly allocated in a ratio of 1:1 to receive l-carnitine or placebo with a block size of four. Allocation sequence will be determined by sequence in permuted blocks of four. A block size of four is constructed 6 different block to assign patients to the trial groups as follows equally:

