#### Concealment mechanism {16b}

Sealed, opaque envelopes prepared by the supplement manufacturer, along with similar pill boxes that only varied in label (A or B) containing capsules will be used. These are provided to the MK without specifying which package is the l-carnitine or the placebo. The content of envelope determines A or B.

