#### Implementation {16c}

Generation of the allocation sequence will be implemented by second investigator (BA) of study and enrollment of participants, and assignment of participants to intervention or control group will be done by the MK.

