### Assignment of interventions: blinding

#### Who will be blinded {17a}

l-carnitine and placebo pill boxes will be tagged A and B by the food supplement company (Karen Co.) along with opaque and sealed envelopes, and will be prescribed to participants with a double-blind method. Note that patients or their legal guardians, researchers, and data analysts will be blinded. The data coordinator and trial steering committee will have access to group allocations by accessing to concealment sealed envelopes.

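### Two shared letters (A/B) in fixed, published blocks of four let the enrolling investigator predict the next letter, and decoding one letter would reveal all 60 assignments

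*Protocol article*

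**What the plan says.** **Sequence.** Under Sequence generation {16a}: "Eligible patients will be randomly allocated in a ratio of 1:1 to receive l-carnitine or placebo with a block size of four", then "Allocation sequence will be determined by sequence in permuted blocks of four". Six distinct blocks are said to be in use. The section mentions no other block size and no stratification.

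**Codes.** Under Concealment mechanism {16b}, "similar pill boxes that only varied in label (A or B) containing capsules will be used", and "The content of envelope determines A or B". The enrolling investigator receives the boxes without being told which letter is l-carnitine.

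**Roles.** Under Implementation {16c}, the second investigator generates the sequence, and one other investigator both enrols and assigns. Under Strategies to improve adherence {11c}, the enrolling investigator also gives the capsules, and the second investigator counts them daily. Setting {9} names one hospital.

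**Envelopes and access.** {16b} refers to "Sealed, opaque envelopes prepared by the supplement manufacturer". Who will be blinded {17a} lists patients or guardians, researchers and analysts as blinded. It adds, "The data coordinator and trial steering committee will have access to group allocations", by means of the sealed envelopes. Procedure for unblinding {17b} has the company's envelopes opened after the analysis to reveal the labels, and says any unblinding will be reported.

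**The concern.** Sealed envelopes hide the next slip of paper. They do not hide what the earlier letters imply about it. With a constant, known block size and a visible letter history, the person deciding on entry can count within the block.

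Two shared letters add a second weakness. Blinding is not protected patient by patient, because the whole trial rests on one secret: which letter is active. The protocol itself names ways this could leak. Adverse event reporting {22} gives fish odour and diarrhoea as possible effects of l-carnitine, and {17a} gives two parties access to allocations.

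The stake is selection. Eligibility criteria {10} include judgements such as severe and progressive sepsis or expected inability to take enteral feeding. They also list unwanted side effects after dosing as grounds for exclusion. {11c} removes patients who took less than 80% of capsules. Someone who believes they know a patient's treatment could influence entry or removal, and with 30 per group a few such decisions can matter.

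**Working it through.** **Inputs.** 1:1 allocation and block size 4 ({16a}); 60 patients (Sample size {14}); one site ({9}); one enroller who sees the letters ({16b}, {16c}, {11c}). Assumption: the enroller remembers past letters and knows where each block starts.

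**The plan's own figure.** Blocks with two A and two B: C(4,2) = 6, which agrees with {16a}. 60 / 4 = 15 complete blocks.

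**Letters certain in advance.** The next letter is certain once two of the same letter have appeared in the current block.

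| Block | Certain letters | Expected correct guesses (of 4) |
|---|---|---|
| AABB | 2 | 2.5 |
| BBAA | 2 | 2.5 |
| ABAB | 1 | 3 |
| ABBA | 1 | 3 |
| BAAB | 1 | 3 |
| BABA | 1 | 3 |
| Total of 24 | 8 | 17 |

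- By position, the probability of certainty is 0, 0, 1/3, 1. The average is (4/3)/4 = 1/3.
- Over 15 blocks: 15 × 4/3 = 20 of 60 expected. Each block gives 1 certain letter, plus a second with probability 1/3. The SD is √(15 × 1/3 × 2/3) = 1.8, and the possible range is 15 to 30.

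**Best guess.** Guess the letter that is behind in the block, and toss a coin when level.

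- Position 1: 1/2. Position 2: 2/3. Position 3: (1/3)(1) + (2/3)(1/2) = 2/3. Position 4: 1.
- Average: (1/2 + 2/3 + 2/3 + 1)/4 = 17/24 = 70.8%, against 50% with no information.

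**Would other block sizes cure it?** Fixed blocks by exact enumeration. Mixed blocks by simulation of 1,500 sequences of 60, with sizes 4 and 6 equally likely and the enroller knowing both sizes but not their order.

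| Scheme, letters visible | Certain | Best guess right |
|---|---|---|
| Fixed 4 (plan) | 33.3% | 70.8% |
| Fixed 6 | 25.0% | 68.3% |
| Fixed 8 | 20.0% | 66.6% |
| Mixed 4 and 6 | about 5.5% | about 69% |

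Mixing sizes removes most of the certainty but little of the guessing advantage. That advantage comes from the visible letters.

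**Reach of one decoding.** With shared letters, knowing one patient's product fixes the meaning of both letters, so 60 of 60 are revealed. With a unique number per kit, 1 of 60 is revealed.

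**The case against.** The strongest reply is that A/B coding with permuted blocks is a legitimate, common design, and that the protocol does protect it. The enroller is not told what the letters mean, the capsules match, and the labels are revealed only after the analysis. Selecting by an undecoded letter has no consistent direction in favour of l-carnitine. That stands, and it limits the point. Four stronger readings are tempting, and the documents do not support them.

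- **That one treatment in three is known in advance.** Only the letter is. Directional bias also needs a correct belief about what a letter means. The protocol gives no rate for fish odour, and diarrhoea is a poor marker in patients for whom uncontrolled diarrhoea is already an exclusion condition.
- **That {16b} and {16c} contradict each other on who makes the sequence.** Generating a list and packing envelopes from it are separate tasks. The hand-over is unclear, and so is whether the envelopes hold the patient sequence or the key to the letters: {16b} uses envelopes to assign, while {17b} opens them after the analysis. Unclear is not contradictory.
- **That opening envelopes after the analysis is the only access described.** {17a} gives the data coordinator and steering committee another route, and {17b} provides for reporting any unblinding.
- **That outcome measurement is compromised.** The primary outcomes are laboratory assays and 28-day mortality is objective. Assessors are said to be blinded, and a separate blinded researcher enters the data.

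Recruitment within 24 hours of diagnosis also makes it hard to hold a patient back for a preferred slot, though it does not prevent declining one.

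**Conclusion.** The weakness is real and moderate, and it concerns concealment and blinding rather than the analysis. As written, the next letter is certain for an expected 20 of 60 patients and guessable 71% of the time. One correctly decoded letter would turn this into knowledge of treatment for the whole trial. The figures assume that the enroller tracks letters and block boundaries, which is easy with one site, one enroller and no stratification stated. Decoding is a risk, not something the plan foresees. The main exposure is selection at entry and exclusion afterwards, and the documents give no basis for putting a number on the resulting bias. The sample size calculation is unaffected.

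**What to change.** Before the first patient:

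1. Have the manufacturer pack 60 identical kits numbered 01 to 60, with no A/B letter, and dispense them in numerical order.
2. Fill them from a list generated and held by a party with no role in enrolment, dosing or capsule counts, for example the manufacturer. This replaces the second investigator, who now generates the sequence and also counts capsules.
3. Keep one sealed code-break per kit number, so that opening one reveals one patient.
4. State in {16b} to {17b} who generates and holds the list, what the envelopes contain, and how the access given in {17a} works under kit numbers.

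Varied block sizes may be added, but they gain little once the letters are gone.

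The cost is minor extra packing and labelling, and a new list. Trial status gives version 1.0 as June 2021 with recruitment from September 2021, so on those dates the change fits before enrolment. Outcomes and sample size stay as they are.

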#### Concealment mechanism {16b}

Sealed, opaque envelopes prepared by the supplement manufacturer, along with similar pill boxes that only varied in label (A or B) containing capsules will be used. These are provided to the MK without specifying which package is the l-carnitine or the placebo. The content of envelope determines A or B.

#### Implementation {16c}

Generation of the allocation sequence will be implemented by second investigator (BA) of study and enrollment of participants, and assignment of participants to intervention or control group will be done by the MK.

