#### Strategies to improve adherence to interventions {11c}

MK will implement the trial and prescribe drugs orally or via enteral tube feeding and another investigator (BA) ask him to return the pill box daily and will check the number of capsules into the pill box. At the end of the study, if the patients received less than 80% of capsules, he/she will be excluded from the study.

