#### Interim analyses {21b}

An independent statistician will carry out an interim analysis (the logistic regression model) for safety and adverse events when we have reached 50% of the events between two groups. Then, the results will be evaluated by the trial steering committee.

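### The investigator who generates the A/B allocation list also meets the enrolling investigator every day, so concealment depends on a working team member not sharing the list

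*Protocol article*

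**What the plan says.** Five places in the protocol article bear on this.

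- **Implementation {16c}:** "Generation of the allocation sequence will be implemented by second investigator", while "assignment of participants to intervention or control group will be done by the" principal investigator, who also enrols.
- **Strategies to improve adherence {11c}:** the principal investigator gives the capsules. The second investigator, identified by the same initials as in {16c}, will "ask him to return the pill box daily and will check the number of capsules into the pill box". The section then sets a rule: "if the patients received less than 80% of capsules, he/she will be excluded from the study".
- **Concealment mechanism {16b}:** "Sealed, opaque envelopes prepared by the supplement manufacturer", together with look-alike boxes that differ only in the label A or B. The principal investigator is not told which letter is the active product.
- **Who will be blinded {17a}:** "Note that patients or their legal guardians, researchers, and data analysts will be blinded". The only parties given access to group allocations are the data coordinator and the steering committee.
- **Interim analyses {21b}:** "An independent statistician will carry out an interim analysis". No other task is given to this statistician.

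**The concern.** Concealment means that the person deciding whether to enrol the next patient cannot learn what that patient would be assigned. The protocol gives generation and enrolment to two different people, which is the right start. It then brings those two people together every day over the study boxes. The sealed envelopes protect the next assignment only as long as the list-maker passes nothing on, even by accident.

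Masked letters reduce the danger but do not remove it. Every patient carries one of only two codes, so a correct suspicion about one patient's product applies to everyone with that letter. Adverse event reporting {22} itself names diarrhoea and a fish odour as possible effects of l-carnitine, so such a suspicion could arise. From then on, knowing the next letter would be enough to influence who is enrolled and when. What is at stake is the comparability of two groups of 30 at entry.

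**Working it through.** The point concerns roles and the plan attaches no figure to it, so the check sets the sections side by side. One short calculation shows that the issue is separate from block size.

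**1. Is it the same person?** Yes. {16c} and {11c} give the same initials for the list-maker and the capsule counter.

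**2. Does that person meet the enroller?** Yes, daily. {11c} has the second investigator ask the principal investigator for the box each day, and {16c} makes the principal investigator responsible for enrolment and assignment.

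**3. Does the list-maker know the list?** This is an inference, though a natural one: whoever generates a sequence has seen it unless a step prevents this, and none is described. It is sound for the sequence of A and B, since {16b} says that the envelope content determines the letter. It does not extend to the key linking letters to products. {16b} withholds that key from the principal investigator, and the unblinding section {17b} keeps it in the company's envelopes until after the analysis.

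**4. Is this access acknowledged?** No. {17a} names two parties with access to allocations, and the list-maker is neither.

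**5. Is it only the block-size issue under another name?** No. Sequence generation {16a} uses permuted blocks of four, 1:1, which gives six possible blocks. Suppose someone knows the block size and sees the earlier letters in the block.

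- Position 1: the chance of a correct guess is 1/2.
- Position 2: the opposite letter is right with chance 2/3.
- Position 3: certain if the first two letters match (chance 1/3), otherwise 1/2. This gives 1/3 + (2/3 × 1/2) = 2/3.
- Position 4: certain.

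The average is (1/2 + 2/3 + 2/3 + 1)/4 = 0.708. Allocations fully determined in advance: position 4 in all 6 blocks and position 3 in the 2 blocks that open with a matching pair, so (6 + 2)/24 = 1/3. A good guesser is therefore right about 71% of the time, whereas a person holding the list is right for all 60 patients. Varying the block size would lower the first figure and leave the second unchanged.

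**The case against.** The strongest reply is that the essential separation already exists. One person generates and another enrols, the envelopes are sealed, opaque and made up by the manufacturer, and the letters are masked. How the list travels to the manufacturer, and whether the investigator keeps a copy, are operational details that an article may leave to the full protocol. Much of this stands: it makes the fault small, and the missing details are not counted against the plan here. It does not remove the point, because the combination of roles is what the article itself states.

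A reader might go further in three ways that the documents do not support.

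- **That the blinding statement is contradicted.** Blinding here concerns which letter is l-carnitine. Nothing says that the second investigator holds that key, and knowing a string of letters is a matter of concealment. What does need aligning is the narrower sentence on who has access to allocations.
- **That the list-maker could bias the 80% exclusion.** The boxes show A or B to whoever counts, list or no list. The rule is numerical: 3 capsules × 7 days = 21, and 80% of 21 is 16.8, so it applies below 17 capsules. {11c} names nobody as deciding the exclusion.
- **That a shift in mean CRP can be calculated from it.** The specimen section {33} places the study assays after all specimens are collected, so the documents do not give the counter study CRP values to act on. Any such figure would rest on an invented pattern of exclusions.

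It can also be objected that handing the list to the interim statistician gives it to an analyst, while {17a} says that analysts are blinded. That is a fair limit on the remedy, and the fix below allows for it.

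**Conclusion.** The point holds as a modest weakness in allocation concealment. One working team member can know all 60 upcoming letters while meeting the enrolling investigator daily, and the list of those with access to allocations omits that person. The conclusion assumes that the generator sees and can retain the sequence, which the article implies but does not state. No bias is demonstrated and no effect on the CRP comparison can be quantified. The change is desirable rather than critical, and it is worth making because it is cheap and because concealment cannot be restored for patients already assigned.

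**What to change.** In Implementation {16c}, assign generation of the list to someone with no part in daily conduct, enrolment or outcome analysis. State that this person sends it directly to the manufacturer for the envelopes, and that neither the principal nor the second investigator holds or sees it. The independent statistician of {21b} is a possible choice, provided that the list contains only the letters A and B and that this person takes no part in the outcome analysis. An interim comparison of the two groups needs the letters in any case, so holding a coded list would add little to what that person learns.

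In {17a}, name the list generator and the manufacturer among those who hold the allocation sequence, so that the access statement matches {16c}. The second investigator can keep the capsule count, because the weakness does not lie there.

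The cost is a sentence or two and one reassigned task before the envelopes are made up, plus a small amount of the generator's time. No extra person is needed if the interim statistician takes it on.

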### Assignment of interventions: blinding

#### Who will be blinded {17a}

l-carnitine and placebo pill boxes will be tagged A and B by the food supplement company (Karen Co.) along with opaque and sealed envelopes, and will be prescribed to participants with a double-blind method. Note that patients or their legal guardians, researchers, and data analysts will be blinded. The data coordinator and trial steering committee will have access to group allocations by accessing to concealment sealed envelopes.

#### Procedure for unbinding if needed {17b}

After implementing statistical analyzes, we will open Karen supplement company envelopes to reveal labels. Any unbinding will be updated on Iranian Registry of Clinical Trials and reported.

### Data collection and management

#### Plans for assessment and collection of outcomes {18a}

Inflammatory biomarkers will be evaluated with ELISA assay method (CRP, ESR, and LDH), oxidative stress will be determined by spectrophotometric methods using commercial kits, and BUN, creatinine, and Alb will be measured at the Clinical Chemistry Laboratory in Al-Zahra hospital, according to a standardized protocol. Anthropometric variables also will be evaluated by MK according to the mentioned formula using a tape meter.

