**Method and design:**

In this double-blind, randomized controlled clinical trial, we will use block randomization of 60 patients with sepsis, aged between 20 and 65 years from Al-Zahra Hospital, Isfahan, Iran. The intervention group (*n* = 30) will receive three capsules of l-carnitine (each capsule contains 1000 mg l-carnitine; totally 3000 mg/day) for 7 days, and a control group (*n* = 30) will receive a placebo with the same dose and for the same duration in addition to usual care. At baseline, scores for clinical and nutritional status (Acute Physiology and Chronic Health Evaluation II (APACHE II), Sequential Organ Failure Assessment (SOFA), Quick SOFA (qSOFA), and NUTRIC Score) will be assessed. At beginning and end point of the study, inflammatory markers (CRP, erythrocyte sedimentation rate (ESR)), oxidative stress status (total oxidative stress (TOS), total antioxidant capacity (TAC)), and clinical variables will be evaluated also. The mortality rate will be assessed within 28 days of the beginning of the intervention.

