### Additional consent provisions for collection and use of participant data and biological specimens {26b}

In the written informed consent, we include additional item for getting permission for future research opportunities which participants can say no and only taking part to main study.

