#### Outcomes {12}

All assessors in this trial will be blinded to intervention allocation.

Serum CRP and ESR as an inflammatory agent, serum lactate dehydrogenase (LDH) as a marker of cell injury, total oxidative stress (TOS), and total antioxidant capacity (TAC) as an oxidative stress biomarker will be measured as our primary outcomes. Secondary outcomes include evaluating duration of hospitalization (days) and 28-day mortality rate, differences in albumin (Alb), alanine aminotransferase (ALT), aspartate aminotransferase (AST), blood urea nitrogen (BUN), and creatinine in blood. Anthropometric variables such as weight, height, body mass index (BMI), mid arm circumference (MAC), and calf circumference will be appraised at baseline.

Estimation of patient height: Due to the limitations in the ICU, the patients’ height is calculated based on the following formula [22]:
$$ \mathrm{Height}\ \left(\mathrm{cm}\right)=153.492-\left(7.97\times \mathrm{sex}\ \left[\mathrm{sex}:\mathrm{man}=1,\mathrm{woman}=2\right]\right)+\left(0.974\times \mathrm{ulna}\ \mathrm{length}\ \left[\mathrm{in}\ \mathrm{cm}\right]\right) $$

Estimation of patient weight: Due to the limitations in the ICU, the patients’ weight is calculated based on Chumlea I formula [23]:
$$ \mathrm{Men}:\left(\mathrm{MAC}\times 2.31\right)+\left(\mathrm{calf}\ \mathrm{circumference}\times 1.50\right)-50.10 $$$$ \mathrm{Women}:\left(\mathrm{MAC}\times 1.63\right)+\left(\mathrm{calf}\ \mathrm{circumference}\times 1.43\right)-37.46 $$

Blood drawing will be executed at baseline and end of the trial. About 10 ml volume of fasted blood (at 6:00 o’clock before first meal) will be collected and then centrifuged, with the serum separated from the sediment, and preserved at temperature of − 20 °C.

Calf circumference method of measurement: The circumference of the leg muscle is measured so that the patient is in the supine position. The patient’s left knee rises high enough to form a right corner between the thigh and the leg. We place the tape around the leg muscle and move it along the leg muscle to meter the largest circumference without any pressure to the subcutaneous tissue [24].

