#### Plans for collection, laboratory evaluation, and storage of biological specimens for genetic or molecular analysis in this trial/future use {33}

Blood samples will be collected by investigators, will be labeled with subject ID, and then immediately will be sent to the central laboratory (Alzahra Clinical Research Laboratory, Isfahan) for keeping in − 80 °C freezers. After collecting all specimens, laboratory assessment methods will be executed. Storing of biological specimen will be done only if participants accept the secondary informed consent. No genetic studies are currently planned.

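### ESR, one of five declared primary outcomes, cannot be obtained by the stated method; the storage temperature and the scope of the second consent also need reconciling

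*Protocol article*

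**What the plan says.** All references are to the protocol article.

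- **Primary outcomes.** Outcomes {12} names "Serum CRP and ESR as an inflammatory agent, serum lactate dehydrogenase (LDH) as a marker of cell injury", adds total oxidative stress (TOS) and total antioxidant capacity (TAC), and closes the list with "as an oxidative stress biomarker will be measured as our primary outcomes". That makes five: CRP, ESR, LDH, TOS and TAC. The abstract's method paragraph spells ESR out: "inflammatory markers (CRP, erythrocyte sedimentation rate (ESR".
- **Assay method.** Plans for assessment and collection of outcomes {18a}: "Inflammatory biomarkers will be evaluated with ELISA assay method (CRP, ESR, and LDH". The same sentence gives TOS and TAC to spectrophotometry, and BUN, creatinine and albumin to the hospital's clinical chemistry laboratory.
- **Specimen handling.** Outcomes {12} describes a draw of about 10 ml at baseline and at the end, centrifugation, and "serum separated from the sediment, and preserved at temperature of" −20 °C.
- **Storage and timing.** The section on specimens {33} sends samples at once to the central laboratory's −80 °C freezers. It then says "After collecting all specimens, laboratory assessment methods will be executed", and next "Storing of biological specimen will be done only if participants accept the secondary informed consent".
- **Optional consent.** Additional consent provisions {26b} describes an extra item on future research, for which "participants can say no and only taking part to main study".

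**The concern.** The method named for ESR does not measure ESR. This is more than a detail that an article leaves to a laboratory manual: the article states a method, and the method is wrong. If site staff follow it, a primary outcome is missing for every patient. It could not be recovered later, because frozen serum contains no red cells.

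Two wording problems touch the other primary outcomes less severely. The assays are batched after the last specimen, so they depend on storage, yet the storage sentence is tied to a consent that may be refused. And two different temperatures are given for samples that would wait months before assay.

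**Working it through.** The point is textual, so the check sets the sections side by side. Arithmetic is needed only to fix its extent.

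**1. Can the stated route yield ESR?**
- What is measured: the rate at which erythrocytes settle (the abstract's own expansion of the abbreviation).
- Stated method {18a}: ELISA, which quantifies an analyte in a sample. A settling rate is not an analyte.
- Stated specimen {12}: serum, separated from the sediment. The cells whose settling is to be timed have been removed.
- Other route in the text: none. {18a} names the clinical chemistry laboratory for BUN, creatinine and albumin only, and no whole-blood tube or same-day reading is described.

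Method and specimen each rule ESR out.

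**2. How far does the error reach?**
- Outcomes: 1 of 5. CRP, LDH, TOS and TAC can in principle be assayed from stored serum.
- Readings, if the text is followed literally: 60 patients × 2 draws = 120 planned ESR readings, all of them lost.
- Sample size {14}: the calculation uses CRP alone. It reproduces: 2 × (1.96 + 0.84)² × 37² / 30² = 2 × 7.84 × 1369 / 900 = 23.85, so 24 per group, raised to 30 for dropout. ESR does not enter it, so the figure is unaffected.

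**3. Does the consent wording conflict with the primary assays?**
- {33}: assays run once all specimens are in, so a sample must be stored to be assayed.
- {33}: storage takes place only with the secondary consent.
- {26b}: that consent may be declined by someone who stays in the main study.

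Taken literally, someone who declines remains in the trial without a stored sample for the batched assays. Against this, {26b} ties the optional item to future research, and the opening sentence of {33} sends samples to the freezer without any condition. The text therefore permits two readings. The document gives no refusal rate, so no loss can be calculated.

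**4. Do the temperatures agree?**
- {12}: −20 °C. {33}: −80 °C, with immediate dispatch.

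They differ, and no sequence of steps linking them is described.

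**The case against.** **The ESR wording is probably a slip.** One condensed sentence in a journal article groups three markers under one technique. Tube types are commonly left to a manual, and Outcomes {12} does not forbid a separate whole-blood tube. The hospital laboratory may well run ESR in the usual way. This stands as a likely explanation, and it means that loss of all readings follows only if the text is carried out literally. It does not make the text right. Nor would the multiple imputation planned in {20c} help, since an outcome missing for everyone leaves no observed values to impute from.

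**Three stronger readings are tempting and are not supported.**
- A reader might infer that the specimen plan cannot deliver the primary outcomes as a group. Only ESR fails as written. CRP, which the sample size section calls the main outcome, can be assayed from stored serum.
- A reader might infer that those who refuse the second consent will have no primary data. The heading of {33} includes future use, {26b} links the optional item to future research, and the sentence after the consent condition in {33} concerns genetic studies. The condition was quite possibly meant only for retained material. Loss of trial data is a possible misreading of a loose clause and not a shown consequence, and any figure for it would rest on an invented refusal rate.
- A reader might infer that mixed storage will degrade the oxidative-stress measurements. The article states two temperatures; it does not say that samples will be divided between them. Initial freezing followed by transfer is conceivable, although immediate dispatch speaks against it. Nothing suggests that the arms would be handled differently, and the document gives no basis for the size of any error.

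**Conclusion.** The point holds for ESR: one of five declared primary outcomes is assigned a method and a specimen that cannot produce it. Carried out literally, that affects all 60 patients and both time points. The conclusion assumes only that the sections mean what they say, since the article describes no other ESR procedure. It does not extend to CRP, LDH, TOS or TAC, and it leaves the calculation of 24 per group (30 with dropout) as it is.

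The two storage temperatures are a plain contradiction with no demonstrated effect on results. The consent clause is ambiguous, and on one reading it would block primary assays for those who refuse; it needs clarifying, and no loss can be attributed to it from this document. The ESR correction should come before the first blood draw, because a whole-blood reading that is missed cannot be made up afterwards.

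**What to change.** - **ESR.** In {18a}, remove ESR from the ELISA list and state that it is read on fresh whole blood on the day of each draw. In {12}, describe that tube separately from the serum sample and stop labelling ESR as a serum measure. Cost: one extra tube at each of the two existing draws (2 per patient, at most 120 in all) and same-day laboratory handling.
- **Storage temperature.** Give one value in {12} and {33} and apply it to all samples. If two successive steps are intended, say so and give the time allowed for each. Cost: wording.
- **Consent.** In {33}, state that storage until the planned trial assays falls under the main consent, and that the secondary consent covers only retention for future research. Align {26b} and the consent form. Cost: wording, plus ethics review of the revised form.
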